### Sensitivity analysis

Retrospective and prospective data analysis: In another model, we will not exclude patients with presence of CVD at baseline. The rationale for this is as follows: if HIV patients experience premature CVD, as we hypothesize, and since HIV patients enter the cohort after varying durations of HIV infection, the risk of CVD associated with HIV might be underestimated if patients with prevalent CVD are excluded from the analysis, i.e.: we would “miss” the earlier events occurring in the HIV infected patients before their entry into the cohort.

In this model, HIV infection will remain the main ‘exposure’, but time 0 will be defined as birth date. HIV infection will be coded in a time-dependent manner: “0” for the time before HIV infection in HIV-infected participants and for HIV-negative controls throughout follow-up, and “1” following first HIV diagnosis in HIV-infected individuals. Incidence of CVD will be modeled using time-to-event statistical methods, as described above, with the first incidence of CVD occurring before cohort entry for patients with prevalent CVD at baseline. Dates of CVD occurrence for patients with prevalent CVD at baseline will be obtained retrospectively (at the baseline visit, through pre-planned data collection for complete medical history). Patients will be right-censored at the earliest of times of: loss to follow-up, administrative end of the study or a non-CVD death**.**

Effect of HIV on the risk (hazard) of incident CVD will be adjusted for “standard confounders”: sex, ethnicity, education level, and income (coded as constant over time), as well as smoking, illicit drug use, sedentary lifestyle, and BMI (coded as time dependent variables). Period of prospective cohort participation (coded in a time-dependent fashion as 0/1) will also be added as a potential confounding variable, as being prospectively followed and assessed for CVD will be likely to increase CVD detection.

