### Study participants

***HIV-infected:*** All individuals living with HIV (as defined by a positive serology for HIV) followed in the HIV clinics of the participating centers, as well as all newly infected or newly diagnosed participants meeting inclusion criteria will be offered to take part into the cohort. ***HIV-uninfected***: HIV-seronegative individuals will be selected from among i)healthy individuals from the general population, reached through publicity campaigns, HIV prevention clinics and participating community members. ii) HIV-uninfected individuals followed at the participating clinics and hospitals. The HIV-negative participants will be frequency matched for age, sex and smoking status, but no individual matching will be done. This will be achieved through periodic comparisons of age and sex distributions of the HIV-positive and HIV-negative participants (every 6 months during the enrollment period) and adjustments in study publicity targeting the HIV-negative group.

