### Statistical considerations

#### Power calculation

Based on data from both our local HIV database and our pilot study [27, 28], we expect the HIV positive population to be 80% male, with a mean age of 50 years at the beginning of the study. Based on data from the Framingham study, expected rates of our primary outcome in HIV-negative participants are 10/1000 person-years for men and 4/1000 person-years for women in the 45–54 age group [29]. The rates more than double for the 55–64 age group [29]. Accordingly, we assume the overall CVD incidence rate in HIV-negative controls will range between 8/1000 PY and 12/1000 PY. Analysis for the primary outcome will be limited to subjects who are free of CVD at baseline. We expect that, at baseline, up 10% of HIV- and 15% of HIV+ subjects will have prevalent CVD [29]. Finally, we assume that an average CVD-free subject will contribute 4 years of follow-up (of the maximum potential follow-up of 5 years). Under these assumptions, the recruitment of 1000 subjects in each group (implying that 900 HIV- and 850 HIV+ subjects will be free of CVD at baseline, contributing 3600 and 3400 PY of follow-up) will yield 80% power with alpha = 0.05 to detect hazard ratios of 1.72 to 1.90 for the primary composite outcomeof CVD. These risk increases are clinically plausible and are actually lower than the more than 2-fold (HR > 2.0) increases in the risk of major CVD events associated with HIV infection [30]. Some studies have reported higher HRs for specific sub-populations or CVD events, e.g. HR 4.0 for risk of stroke among younger subjects [31]. All sample size calculations were done with the PASS software [32].

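### The birth-origin sensitivity analysis pools survivor-only pre-entry CVD and prospective CVD in one HIV hazard ratio, which is reliable only if survival and enrolment after CVD do not differ by HIV status

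*Protocol article*

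**What the plan says.** The protocol article's Sensitivity analysis section adds a model that keeps people who already have CVD at baseline. The reason given is that excluding them could understate the HIV effect, because early events in HIV+ people would be missed. In this model "time 0 will be defined as birth date", and HIV status switches from 0 to 1 at first diagnosis. For events before enrolment, "Dates of CVD occurrence for patients with prevalent CVD at baseline will be obtained retrospectively", from the medical history taken at the baseline visit. A time-dependent 0/1 term marks prospective participation, and the only justification offered is better detection of CVD during follow-up. Smoking, illicit drug use, sedentary lifestyle and BMI enter as time-dependent covariates. The section describes no HIV-by-period interaction, no delayed entry and no period-specific HR.

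Three other sections bear on this:
- **Inclusion criteria:** participants must be able to consent and be expected to live at least a year.
- **Primary outcome:** the composite includes cardiovascular death.
- **Study participants:** HIV+ people come from the HIV clinics. Controls come partly from "healthy individuals from the general population, reached through publicity campaigns", from HIV prevention clinics and through community members, and partly from HIV-uninfected patients of the participating clinics and hospitals.

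**The concern.** Everyone is counted at risk from birth, yet a person is in the data only if alive and enrolled, at a mean age of about 50. Fatal CVD before entry can never be recorded. Non-fatal CVD before entry is recorded only if the person survived it and then joined. The pre-entry and post-entry endpoints therefore differ, and the pre-entry data are selected on what happened after the event. One coefficient covers both.

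The period term is a main effect. It raises or lowers the hazard by the same factor in both groups, so it can absorb under-recording that is common to both but not loss that differs by HIV status. The two groups enter by different routes, and survival after CVD may differ too.

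A smaller point concerns BMI. The Covariates and data collection section has height and weight recorded at the baseline visit, which for a prevalent case is after the event. Using that value over pre-entry time adjusts for something measured after the outcome.

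At stake is how the comparison with the primary result is read. What this model adds to the primary analysis is the pre-entry data, so a shift in the HR would largely reflect those selected data.

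**Working it through.** **Inputs (Power calculation section).** The control rate is stated as: "we assume the overall CVD incidence rate in HIV-negative controls will range between 8/1000 PY and 12/1000 PY". Person-years are 3600 (HIV-) and 3400 (HIV+). On prevalent disease the plan expects that "up 10% of HIV- and 15% of HIV+ subjects will have prevalent CVD". With 1000 per group this is up to 100 + 150 = 250 pre-entry first events.

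**Step 1: the plan's own figure.** The plan states that its sample "will yield 80% power with alpha = 0.05 to detect hazard ratios of 1.72 to 1.90". Expected events = 3600r + 3400r × HR.
- r = 0.008, HR 1.90: 28.8 + 51.7 = 80.5.
- r = 0.012, HR 1.72: 43.2 + 70.2 = 113.4.

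Freedman's formula, with alpha taken as two-sided (the article does not say), needs 82 and 113 events. Power is 79.5% and 80.5%, so the figure reproduces and these event counts are a sound base.

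**Step 2: share of events before entry** = pre-entry / (pre-entry + prospective).

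| Prevalence | 8/1000, HR 1.90 | 12/1000, HR 1.72 |
|---|---|---|
| Upper values (250 events) | 250/330.5 = 75.6% | 250/363.4 = 68.8% |
| Half, same person-years (125 events) | 125/205.5 = 60.8% | 125/238.4 = 52.4% |
| Half, with the extra CVD-free people followed | 125/211.6 = 59.1% | 125/247.0 = 50.6% |

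The last row uses 950 and 925 CVD-free people at 4 years each, so 3800 and 3700 PY. Prospective events are then 30.4 + 56.2 = 86.6 and 45.6 + 76.4 = 122.0.

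**Step 3: does the period term protect the pooled HR?** A source population was simulated with a CVD hazard of 10/1000 at age 52 rising by a factor exp(0.08) per year, a constant HIV effect from diagnosis (true HR 1.72) and 5 years of follow-up. Pre-entry cases were lost before enrolment with a probability that depended on HIV status at the event. The model used the age scale with the period main effect. The loss probabilities are assumptions; the documents give none.

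| Loss, HIV- / HIV+ cases | Pooled HR | Pre-entry part | Prospective part |
|---|---|---|---|
| 0% / 0% | 1.73 | 1.71 | 1.78 |
| 25% / 25% | 1.72 | 1.71 | 1.74 |
| 40% / 40% | 1.71 | 1.73 | 1.69 |
| 25% / 35% | 1.60 | 1.50 | 1.74 |
| 25% / 50% | 1.37 | 1.17 | 1.65 |

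The prospective column does not depend on the loss of pre-entry cases; its spread around 1.72 indicates the simulation error. Without the period term the last two pooled values are 1.63 and 1.40, so the term does not help. With a true HR of 1.0, the same two unequal losses give 0.92 and 0.81.

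A hand check agrees. Selection multiplies the pre-entry HR by roughly the ratio of retained fractions: 1.72 × 0.65/0.75 = 1.49 and 1.72 × 0.50/0.75 = 1.15, close to the simulated 1.50 and 1.17.

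**Step 4: the other direction.** A separate, smaller simulation (1000 per group, 40 replicates, 8/1000 at age 50 rising 8.5% per year) returned 1.88 for a true HR of 1.9 without selection. It returned 2.20 when 30% of controls with prior CVD did not volunteer. That 30% is also an assumption.

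**The case against.** - **The model is not broken as such.** With equal loss it returns 1.71-1.73 for a true 1.72. A reader might infer from the large retrospective share that the analysis cannot correct the bias it targets. That does not follow: a high share is not itself a bias, and the model does recover early non-fatal events. This stands.
- **Pre-entry time is not immortal in the usual sense.** A reader might call it so. It is immortal for death, but non-fatal CVD can occur and is counted there, and HIV is coded 0 until diagnosis, which avoids the usual exposure-related error. Only the narrower point about survivors remains.
- **The 69-76% is an upper-end figure.** The plan gives the prevalences as upper values, and the Study visits section allows a year-8 visit for some, which would add prospective events. This stands.
- **Controls are not only healthy volunteers.** Clinic and hospital patients are recruited too, and could enrich the controls for CVD. So the net direction of any selection is unknown, and the documents do not show that the pooled HR is in fact biased.
- **A post-entry HR already exists.** The primary analysis starts at cohort entry in CVD-free people and adjusts for age, so a delayed-entry HR would use the same events. This largely stands. What is missing is the pre-entry estimate on its own, and both periods in one model so that they can be compared.
- **The article claims little.** It says only that the effect might be underestimated and labels the model a sensitivity analysis; it does not promise a corrected HR. An article may also leave modelling detail to a fuller plan. But this section does set out the time origin, the HIV coding and the period term, and it justifies that term by detection alone.
- **Covariates.** Lifestyle history may be dated in the case report form, which is not shown. The covariate point is therefore kept to BMI.

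**Conclusion.** The point holds in a limited form. The pooled HR joins prospective CVD to a pre-entry endpoint that is non-fatal and seen only in enrolled survivors. On the plan's upper-bound prevalences the pre-entry part supplies up to 69-76% of events, and about 51-61% at half those prevalences. The result can be relied on only if survival and enrolment after CVD do not differ by HIV status, a condition the article neither states nor tests. If it fails, the period term does not help: a true 1.72 becomes 1.60 or 1.37 under the assumed unequal losses, and bias the other way is possible. If HIV+ people survive CVD less often, the error runs towards the null, as does the one the analysis was added to address. The size of any real bias is unknown because every loss figure is assumed. The primary result is unaffected, so this is a worthwhile, cheap improvement and not a fault in the main analysis.

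**What to change.** 1. Keep age as the time scale and add an HIV-by-period interaction to the sensitivity model.
2. Report two HRs: post-entry, with delayed entry into the risk set at age of enrolment, and pre-entry.
3. Define the pre-entry endpoint as non-fatal CVD among enrolled survivors, and label that HR accordingly.
4. Do not adjust pre-entry time for BMI first measured after the event.
5. If a pooled HR is still shown, state that it can be relied on only if survival and enrolment after CVD do not differ by HIV status.

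The cost is one extra model term, some rewording and less apparent precision. The post-entry HR would rest on about 80-113 events in place of about 330-363. Taking standard errors as proportional to 1/√events, its interval on the log scale would be roughly √(363.4/113.4) = 1.8 to √(330.5/80.5) = 2.0 times as wide as the pooled one. No new data collection is needed.

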Power calculations were based on event rates from the Framingham cohort [29]. These rates may not apply to the Canadian population, and may be lower now that aggressive treatment of cardiovascular risk factors is widespread. As such, we may lack power to detect differences in the occurrence of the primary endpoint. However, our power calculations were conservative, aiming to be able to detect HRs for our composite endpoint of 1.72 to 1.90, which is lower than the 2.13 95%CI [1.69–2.63] we observed in our own population [59].

Our study encompasses the entire research spectrum, from collection and analysis of epidemiological data on lifestyle, quality of life and medical co-morbidities to advanced fundamental imaging and immunological research. We have access to detailed epidemiological data, and a biobank with stored cells and plasma. Our team of experts also spans the whole research continuum from clinical to basic science, including community members, health practitioners, specialists in cardiology, immunology, virology, genetics, radiology, and internal medicine, with a balance between clinical and basic scientists. This study structure will allow rapid and in-depth investigations into novel immuno-metabolic pathways that lead to CVD in the setting of HIV infection.

Another important advantage of our cohort setting is the universal health care system that is available to all participants of our study. This will greatly contribute to alleviate discrepancies in healthcare that would be due to socioeconomic status. Central data collection and management is another strength. Overall, flexibility of the study structure, with possible addition of further sub-studies to the main cohort, is a major capacity-building aspect of this cohort.

We believe the Canadian HIV and Aging Cohort Study will be a powerful research tool to offer rapid responses to emerging clinical questions for people living with HIV and their healthcare providers.

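### The birth-origin sensitivity model has no birth-year or calendar-period term, so a calendar trend in recorded CVD rates would be partly attributed to HIV

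*Protocol article*

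**What the plan says.** The Sensitivity analysis section describes a model that keeps participants with CVD at baseline and counts their earlier events. Its stated reason is that excluding them might underestimate the HIV effect. Three features matter here.

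- **Time scale.** "time 0 will be defined as birth date", so risk sets are formed at equal age.
- **Exposure.** HIV is 0 "for the time before HIV infection in HIV-infected participants and for HIV-negative controls throughout follow-up", and 1 "following first HIV diagnosis in HIV-infected individuals".
- **Adjustment.** The fixed covariates are "sex, ethnicity, education level, and income (coded as constant over time"). The time-dependent ones are "smoking, illicit drug use, sedentary lifestyle, and BMI (coded as time dependent variables"). One further term is named: "Period of prospective cohort participation (coded in a time-dependent fashion as 0/1) will also be added as a potential confounding variable". The reason given for that term is better detection of CVD under prospective follow-up.

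Neither birth year nor calendar period is listed. On matching, the Study participants section says: "The HIV-negative participants will be frequency matched for age, sex and smoking status, but no individual matching will be done". On trends, the Discussion says that the Framingham rates used for the power calculation "may be lower now that aggressive treatment of cardiovascular risk factors is widespread".

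**The concern.** A model on age from birth compares people of the same age who reached that age in different decades. Matching on age at enrolment makes the two groups of people similar in birth year. It does not do so for person-time, because the earlier years of HIV-positive participants are coded 0. At any given age, a person already diagnosed is more likely to belong to a later birth cohort. Exposed person-time is therefore more recent than unexposed person-time, and a calendar trend in recorded CVD rates is partly credited to HIV.

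This analysis is meant to show whether the primary analysis understates the HIV effect. If rates have fallen, the omission lowers the very estimate that is supposed to reveal the understatement. The error is systematic, so a larger sample does not reduce it.

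**Working it through.** **1. The plan's own figure.** The plan gives no figure for the sensitivity model. The only related figure is the primary-analysis power: 80% for hazard ratios of 1.72 to 1.90. At 8/1000 person-years and HR 1.90, expected events are 3.6 × 8 + 3.4 × 8 × 1.90 = 80.5. At 12/1000 and HR 1.72 they are 3.6 × 12 + 3.4 × 12 × 1.72 = 113.4. Schoenfeld's formula, with 850 of 1750 exposed and two-sided 0.05, gives power 0.821 and 0.823; Freedman's gives 0.795 and 0.805. The figure reproduces, and this point does not touch it.

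**2. Why exposed time is later at equal age.** A hand example, with all dates assumed: entry in 2014, diagnosis uniform over 1985–2014, and equal numbers aged 60 and 45 at entry in each group. They were aged 40 in 1994 and 2009.

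- HIV-positive people diagnosed by age 40: 9/29 of the older and 24/29 of the younger. Mean calendar year of exposed time at age 40: (9 × 1994 + 24 × 2009)/33 = 2004.9.
- Unexposed: the not-yet-diagnosed (20/29 and 5/29) plus all controls (29/29 each), so weights 49 and 34. Mean: (49 × 1994 + 34 × 2009)/83 = 2000.1.
- Gap at age 40: about 4.8 years, although the two groups have identical ages at enrolment.

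**3. The gap over a realistic age mix.** Inputs from the protocol: mean entry age 50, minimum age 40 for controls, and rates that more than double from ages 45–54 to 55–64. Assumed, because the protocol does not give them: entry from 2011 to 2016 or 2017, the age spread, and several distributions of diagnosis date. With mean age 50, the gap at ages 40 to 55 is about 0.3 to 6 years. Across wider scenarios (mean age 50 or 55, ages 35 to 60) it runs from 0.1 to 10.6 years and is at most 2.1 at age 60. Weighted by events, it is 0.7 to 3.5 years.

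**4. From gap to bias.** If rates fall by a fraction *b* per year and the event-weighted gap is *g* years, the hazard ratio is multiplied by roughly exp(−*b* × *g*). The extremes are exp(−0.01 × 0.7) = 0.99 and exp(−0.03 × 3.5) = 0.90. The full calculation used expected counts in one-year age bands, fitted by Poisson regression with a separate level for each age (equivalent to Cox on the age scale):

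| Assumed yearly fall | Factor, no prospective indicator | Factor, indicator included | Indicator included, applied to a true 1.72 |
|---|---|---|---|
| 1% | 0.97–0.99 | 0.97–0.99 | 1.67–1.70 |
| 2% | 0.93–0.98 | 0.94–0.98 | 1.62–1.69 |
| 3% | 0.89–0.97 | 0.91–0.97 | 1.57–1.67 |

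The last column is 1.72 times the column before it. With no trend the factor is 1.000. With a 1% yearly rise it is 1.015.

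**5. What the planned indicator does.** It acts partly as a recent-period term. At a 2% fall it moves the factor from 0.956 to 0.963 in the base scenario, removing 0.007/0.044 = 16% of the bias. With late diagnoses it moves the factor from 0.937 to 0.955 (0.018/0.063 = 29%), and with early ones from 0.982 to 0.983 (0.001/0.018 = 6%).

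**6. With a birth-year term.** A linear birth-year term returns the hazard ratio to its true value in every scenario run with a calendar trend alone (1.000 for 1.0, 1.900 for 1.9). A linear calendar-year term is equivalent, because calendar year is birth year plus age and age is already the time scale.

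**The case against.** **The direction is not settled.** Events before enrolment are known only for people who survived to enrol, and they are collected retrospectively at the baseline visit. Older events are plausibly under-captured, so recorded rates may rise over calendar time even if true rates fell. With a 2% yearly fall, a true 1.72 is estimated at about 1.64–1.65. If capture of past events also drops by an assumed 2% for each year before entry, the estimate is 1.72; at 3% it is 1.75. This stands. The calendar imbalance is structural, but the sign of the bias depends on the net trend in the recorded data. A reader might infer that the hazard ratio must be too low; the protocol does not support that, since the Discussion says only that rates may be lower and gives no annual rate.

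**The size is modest.** The expected prevalences imply up to 100 + 150 = 250 baseline cases. Adding 80 to 113 incident events gives about 330 to 363. The standard error of the log hazard ratio is then roughly 2/√330 = 0.11. A 9% bias is |ln 0.91| = 0.094, less than one standard error, and a 5% bias is about half of one. This also stands.

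**The covariate set may be left to a fuller plan.** This is weaker. The section lists a set specific to this model and adds a purpose-built time-dependent term, so the point concerns a stated adjustment set. Time-dependent smoking and BMI might absorb a little of the trend; that was not modelled.

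**Conclusion.** The concern holds in a limited form. The listed adjustment set leaves calendar time unbalanced between exposed and unexposed person-time, so any calendar trend in recorded CVD rates leaks into the HIV hazard ratio. Under an assumed fall of 1% to 3% a year, and with the planned indicator included, the estimate would be about 1% to 9% too low. The bias is zero without a trend, and it can cancel or reverse if older events are under-captured.

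Three stronger readings are tempting and not supported:

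- The calendar gap is not a known number of years. The protocol gives neither enrolment dates nor a distribution of diagnosis dates, and the larger gaps occur at ages with few events.
- Adding a calendar term would not make the analysis unbiased. It removes confounding by calendar trend, but it cannot recover fatal events before enrolment.
- The primary result is not at risk. That analysis starts at cohort entry and adjusts for age, and the power calculation is unaffected.

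**What to change.** In the Sensitivity analysis model, stratify by birth cohort (for example 5-year bands), or adjust for birth year or time-dependent calendar period. Keep the prospective-participation indicator, which serves a different purpose. Five-year bands leave a small within-band remainder; a continuous birth-year term does not if the trend is log-linear. In the runs, such a term returned a true 1.72 to 1.72 under a falling trend, and to 1.73 when recall loss was added.

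State alongside the result that the term does not address deaths before enrolment or incomplete recall of older events.

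The cost is one sentence in the plan and one stratum or covariate. Birth date is already needed as the time origin, so there are no new data to collect, and the loss of precision is negligible.
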